### Ethics Compliance

Since the IEO is the promoter of the multicenter pilot study, the research protocol of the multicenter clinical study was first submitted for approval to the Ethics Committee of the IEO. Once approved by this Ethics Committee (approval No. R868/18-IEO 916; approval date: October 24, 2018), the protocol was submitted for approval to the Ethics Committees of HUS, the Rabin Medical Center and the Shaare Zedek Medical Center (under HUJI’s responsibility), and the CHAMP. In the course of the study, an amendment was submitted to the Ethics Committee of the IEO (amendment version No. 1 date: August 12, 2019; approval date: September 18, 2019) and to the centers in which such process was deemed necessary.

The multicenter pilot study has been devised so as to comply with both national (ie, Good Clinical Practices) and international declarations (ie, the Declaration of Helsinki) regulating proper ethical research involving human subjects, with informed consent obtained from all subjects. Specifically, conduction of the trial is in accordance with the following regulation and norms:

The Declaration of Helsinki, ethical principles for medical research involving human subjects, revised October 2013The Convention for the Protection of Human Rights and Dignity of the Human Being with regard to the Application of Biology and Medicine: Convention on Human Rights and Biomedicine, Oviedo 1997The Council for International Organizations of Medical Sciences in collaboration with the World Health Organization, International Ethical Guidelines for Biomedical Research Involving Human Subjects, revised in 2016The Belmont Report: Ethical Principles and Guidelines for the Protection of Human Subjects of Biomedical and Behavioral Research. Department of Health, Education, and Welfare (DHEW) publication (DHEW-05-78-0012), Washington, DC, 1978.

## Results

The recruitment process stared in January 2019 and ended in November 2021. Preliminary results have been published in a scientific journal and are available for consultation on the BOUNCE project website [64]. Data analysis and dissemination of the study results will be performed in 2022.

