**Methods:**

A total of 660 women with breast cancer will be recruited from five European cancer centers in Italy, Finland, Israel, and Portugal. Biomedical and psychosocial variables will be collected using the Noona Healthcare platform. Psychosocial, sociodemographic, lifestyle, and clinical variables will be measured every 3 months, starting from presurgery assessment (ie, baseline) to 18 months after surgery. Temporal data mining, time-series prediction, sequence classification methods, clustering time-series data, and temporal association rules will be used to develop the predictive model.

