Drawing from the theoretical and empirical framework described above, here we describe the study protocol of a multicenter clinical study entitled “Predicting Effective Adaptation to Breast Cancer to Help Women to BOUNCE Back” or, in short, BOUNCE. With this study, we intend to identify psychosocial, biomedical, and functional factors that predict the capacity of individual patients to “bounce back” during the highly stressful treatment and recovery period following a diagnosis of breast cancer (Figure 1 [44]). This study has been designed to investigate resilience trajectories starting at diagnosis and for 18 months of follow-up. The underlying hypothesis is that biomedical, psychosocial, and functional factors may predict trajectories of resilience and adjustment to breast cancer.

If confirmed, this would support the general purpose of the study, which is the early identification of women at risk for whom early intervention (eg, through personalized psychological support) would be necessary. This multicenter clinical pilot study is the core of a larger European Union (EU) project named BOUNCE (grant agreement No. 777167), which has been developed to understand and study resilience through the cancer continuum in patients with breast cancer. The main global goal of the BOUNCE project is to build a quantitative mathematical model of factors associated with the capacity for optimal adjustment to cancer; this will initially be done through a data-driven method, including the computation of resilience on the basis of retrospective data, and through a psychometric method, as described here, with prospective assessment of several domains of resilience through questionnaires.

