## Methods

### Study Design and Clinical Partners

The clinical pilot study has been designed as a longitudinal prospective cohort, with assessments at diagnosis of breast cancer and 3, 6, 9, 12, 15, and 18 months later. It involves different clinical centers in several countries, namely the European Institute of Oncology (IEO) in Italy, Helsinki University Hospital (HUS) in Finland, the Champalimaud Clinical Centre (CHAMP) in Portugal, and the Rabin and Shaare Zedek Medical Centers, coordinated by the Hebrew University of Jerusalem (HUJI) in Israel. Data were primarily collected through the Noona Healthcare platform (Noona), a personal health records system designed for patients with cancer. For those patients who do not want or are unable to use Noona, the paper-and-pencil mode are available. Data are then inserted into the Noona platform by a researcher. Noona is a fully responsive web application that is usable with a web browser on any suitable device that is available to the user, including desktop, laptop, tablet, and smartphone devices. Noona is classified as a medical device; more specifically, it is classified as a web platform designed for patients with cancer for remote monitoring and as a support tool for communication between patients with cancer and health care professionals. However, in the multicenter clinical study, Noona will not be used for communication between the treatment team and patients, but will only be used for the collection of study-relevant information. Thus, the main functionalities, such as reporting symptoms or requesting assistance, will not be taken into consideration. The study was registered at ClinicalTrials.gov (NCT05095675).

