### Time Point Measurements

Psychosocial, sociodemographic, lifestyle, and clinical variables were measured at different time points (Tables 1-3). There were seven assessment time points over a period of 18 months: baseline (ie, just after the diagnosis, before the start of chemotherapy, or within 2 weeks from the start of endocrine therapy) and every 3 months until month 18. Each assessment time point contains a set of specific measures that are able to capture salient changes in specific domains. Accordingly, variables that are not sensitive to change (eg, tumor biology and personality trait) were collected only at baseline. Data that are expected to change over time because of intervening factors (eg, starting of treatment and associated side effects, as well as adverse life events) were collected periodically.

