### Recruitment and Follow-Up

A trained researcher identified all eligible patients, evaluating inclusion and exclusion criteria, by checking the patient’s health records stored in the electronic database of the hospital. Successively, during the first clinical consultation, the investigator briefly introduced the study to each eligible patient and collected informed consent from those interested in participating. During this first meeting, the investigator gave a short training in Noona and created the patient account. The investigator could use Noona to monitor the response status of questionnaires for each patient and could contact them to stimulate adherence to the study, completion of the questionnaires, and support for any issues with the platform.

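### The stated dates conflict: recruitment ended in November 2021 with 18 months of follow-up (to about May 2023), yet the study results are to be analysed and disseminated in 2022

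*Protocol article*

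**What the plan says.** The Results section, and the Results paragraph of the Abstract in the same words, give the recruitment period: "The recruitment process stared in January 2019 and ended in November 2021". The same paragraph then gives the timetable for the results: "Data analysis and dissemination of the study results will be performed in 2022".

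Follow-up per woman is fixed in four places:

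- Novelty and Study Aim: "This study has been designed to investigate resilience trajectories starting at diagnosis and for 18 months of follow-up".
- Study Design and Clinical Partners: a prospective cohort "with assessments at diagnosis of breast cancer and 3, 6, 9, 12, 15, and 18 months later".
- Time Point Measurements: "There were seven assessment time points over a period of 18 months".
- Abstract, Methods: measurement every three months, "starting from presurgery assessment (ie, baseline) to 18 months after surgery".

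Interim analyses on extracts taken during the project are described separately, under Statistical Considerations on the Design. The Results section adds that preliminary results have already been published. The article names no data cut-off, no shorter follow-up for late entrants and no analysis after 2022.

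**The concern.** The 2022 sentence comes after separate mention of interim analyses and of preliminary results already published, so it reads as the main analysis. If that analysis is done on the stated dates, the last women enrolled have not finished follow-up.

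This matters because 18-month trajectories are the design aim, and telling trajectories apart is the first secondary objective. Some information exists only late in the schedule:

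- Return to work is collected only at Month 18 (Table 2).
- Relapse, metastatic disease and death are collected only at Months 12 and 18 (Medical and Treatment Information).
- The last Connor-Davidson Resilience Scale is at Month 15 (Table 1).

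If late entrants are analysed before these visits fall due, the series have unequal length for an administrative reason. A reader could not then tell whether the 18-month model rests on complete follow-up.

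**Working it through.** The article gives no date for the end of follow-up, so there is no figure of its own to reproduce. The check is date arithmetic.

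**Inputs from the article**

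- Recruitment from January 2019 to November 2021, which is 12 + 12 + 11 = 35 calendar months (Results).
- Follow-up of 18 months, with visits every 3 months (Study Design and Clinical Partners).
- 660 women recruited (Study Participants).
- Analysis and dissemination in 2022, so the latest possible cut-off is 31 December 2022 (Results).

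**Step 1. Visits of the last recruits.** Visit date = recruitment date + visit month.

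| Visit | Recruited 1 Nov 2021 | Recruited 30 Nov 2021 |
|---|---|---|
| Month 12 | 1 Nov 2022 | 30 Nov 2022 |
| Month 15 | 1 Feb 2023 | 28 Feb 2023 |
| Month 18 | 1 May 2023 | 30 May 2023 |

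Five of the seven assessments (Months 0, 3, 6, 9 and 12) can be reached in 2022. Months 15 and 18 cannot. Complete 18-month data exist from about May 2023, five months after the end of 2022.

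**Step 2. Latest entry with a possible Month 18 in 2022.** 31 December 2022 minus 18 months is 30 June 2021. Women recruited from July to November 2021, the last 5 of the 35 months, have no Month 18 by then. The same subtraction for Month 15 gives the end of September 2021, so October and November 2021 recruits also lack Month 15.

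**Step 3. How many women.** This needs an accrual curve, which the article does not give. Assuming uniform accrual, 660 / 35 = 18.9 women a month:

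- No Month 18 by 31 December 2022: 5 / 35 × 660 = 94 (14%). Counting in days gives 95.
- Neither Month 15 nor Month 18: 2 / 35 × 660 = 38 (6%).

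If the last five months ran at half the average rate, the first figure is 0.5 × 94.3 = 47 (7%). At twice the average it is 2 × 94.3 = 189 (29%). Under uniform accrual, each month by which the cut-off precedes 31 December 2022 adds about 19 women.

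**Step 4. Does the time origin resolve it?** The Abstract counts to 18 months after surgery from a presurgery baseline, which makes the last visit later still. The Methods count from diagnosis. For a November 2021 recruit to reach Month 18 within 2022, diagnosis would have to fall by the end of June 2021, about four to five months before recruitment. That sits badly with consent taken "during the first clinical consultation, the investigator briefly introduced the study to each eligible patient and collected informed consent" and a baseline "just after the diagnosis, before the start of chemotherapy, or within 2 weeks from the start of endocrine therapy". The endocrine-therapy option leaves some room for individual women, but it does not explain the timetable as a whole.

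**Step 5. The alternative reading.** If November 2021 was the end of data collection, full follow-up requires enrolment to have closed 18 months earlier, about May 2020. The 2022 timetable then fits, and the stated end of recruitment is wrong by about 18 months.

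**The case against.** The strongest reply is that the sentence is loosely worded and nothing is lost. Much of the Methods reports data collection in the past tense, including the Month 12 and Month 18 medical data and the notes to Tables 1 to 3. On that view November 2021 is when data collection finished, and analysis in 2022 follows naturally. This is plausible, but it is not established. Tenses are mixed (the Abstract still speaks of recruitment as future), and Study Participants uses recruitment in its ordinary sense of entry at baseline. The reply also concedes that a stated date is wrong.

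Several stronger readings are tempting, and the article does not support them:

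- **Late recruits are cut off by design, or a final lock is set in 2022.** The article does not call the 2022 analysis final, names no lock and does not say that follow-up stops. It allows for analyses on successive extracts. Truncation is what follows from taking the dates literally. It is not a stated rule.
- **A mid-2022 lock leaves fewer than 500 women.** No such lock appears in the article. At the latest cut-off that 2022 allows, 660 − 94 = 566 could have a Month 18 visit before any dropout.
- **With 40% attrition the sample is too small because of the dates.** 660 × 0.6 = 396 is already below 500 with complete follow-up. That is a separate sample-size question.
- **The loss differs by centre.** No centre-specific recruitment dates are given, so this is conjecture.

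The primary objective also concerns prediction at several time points, so analyses through Month 12 are unaffected at a cut-off of 31 December 2022. A lock date and visit windows may well be set out in the full protocol or analysis plan, and their absence here is not the point. The point is that two dates printed in the article cannot both hold alongside the stated follow-up.

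**Conclusion.** The concern holds as an internal contradiction in the timeline. November 2021 plus 18 months is about May 2023, and nothing in the article reconciles that with analysis and dissemination in 2022. This conclusion rests only on the printed dates and the stated follow-up.

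The size is less certain. About 94 of 660 women (14%) would lack Month 18 at the latest 2022 cut-off. That rests on three things: enrolment really ended in November 2021, accrual was uniform, and time zero is close to recruitment. The figure would be larger at an earlier cut-off and zero if November 2021 was the end of data collection. No bias in the results is shown. What is shown is that a reader cannot tell from the article whether the 18-month analyses use complete follow-up.

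**What to change.** Reconcile the dates in the Results section and in the Abstract.

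- **If November 2021 was the end of enrolment**, do one of two things. Either run the 18-month and trajectory analyses after the last Month 18 visit (about May 2023, later if counted from surgery) and label 2022 output as interim, or keep 2022, state a cut-off, restrict the 18-month analyses to women whose Month 18 visit was due before it, and report that number.
- **If November 2021 was the end of data collection**, correct the recruitment sentence and give the true end of enrolment.

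The cost is a final report about five months or more after the end of 2022, a smaller and clearly labelled 18-month set, or a one-sentence correction. No extra patients are needed.

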## Discussion

Due to the increasing interest in the role of resilience in cancer recovery, there is a need for evidence regarding the complex paths between resilience, factors affecting resilience, and the interrelated illness outcomes. The study described here has the advantage of firstly assessing the combination of biological, clinical, lifestyle-related, and cognitive-emotional factors. These multiple variables account for systematic fluctuations of resilience across time that, in turn, actually contribute to successful adaptation to and recovery from breast cancer. BOUNCE aspires to move from a biomedical to a person-centered and biopsychosocial approach, toward growing awareness of the complexity of health and individual responses to illness [64-68]. In particular, we expect that this study will provide a predictive model to describe individual resilience and related factors, with the aim of personalized treatment plans, according to such predictions. In fact, we propose that the identification of individual resilience trajectories along the care process will lead to the development and implementation of tailored interventions, ideally supported by eHealth technologies [69-72]. In addition, it will scale up the knowledge about the interaction between biological, clinical, and psychosocial factors and outcomes, supporting, for example, programs of psychological prevention to support the patient across the disease trajectory.

Data collected from this pilot study could also provide information about cross-cultural differences. Further analyses and research based on BOUNCE data could examine the impact that the various health care systems in different countries could have on breast cancer resilience trajectories. Such possible differences will be of paramount importance, not only for a mere descriptive purpose but also for the development of a culture-based prediction model.

A possible limitation of this study is the large number of self-report scales used to collect the psychosocial variables; this may be perceived as too taxing by patients. However, considering that the general purpose of the study is the early identification of women at risk of poor adaptation, throughout the development of a data-driven quantitative mathematical model, all mentioned variables are needed at this research step to build a unified, multidimensional resilience trajectory predictor tool. This prediction model will encompass the results of the major analyses to be performed within the BOUNCE project; the results will identify potentially different trajectories of psychological adaptation to breast cancer over time, as well as the medical, sociodemographic, and psychosocial variables that may predict these trajectories. Although the final form of this tool is not yet decided and will depend on the actual findings of the study, hopefully it will allow health professionals to have a holistic picture of the patient condition: all the biological, psychological, and social factors together at a glance for a perfectly integrated treatment plan.

## Abbreviations

CHAMP: Champalimaud Clinical Centre
DHEW: Department of’ Health, Education, and Welfare
EU: European Union
EudraCT: European Union Drug Regulating Authorities Clinical Trials Database
FORTH: Foundation for Research and Technology–Hellas
HER2: human epidermal growth factor receptor 2
HUJI: Hebrew University of Jerusalem
HUS: Helsinki University Hospital
ICCS: Institute of Communications and Computer Systems
IEO: European Institute of Oncology
Noona: Noona Healthcare platform
QOL: quality of life
